**Primary outcome**		
	Mental well-being	Mental Health Continuum–Short Form (14 items) [70]
**Secondary outcomes**		
	Depression	Edinburgh Postnatal Depression Scale (10 items) [71]
	Anxiety	Generalized Anxiety Disorder (7 items) [72]
	Stress	Perceived Stress Scale (10 items) [73]
	Self-compassion	Self-Compassion Scale–Short Form (12 items) [74]
	Mindfulness	Mindful Attention and Awareness Scale (15 items) [75]
	Emotion regulation	Difficulties in Emotion Regulation Scale (16 items) [76]
	Affect	Positive and Negative Affect Scale–Short Form (10 items) [77]
	Quality of life	EuroQol–5 Dimension (5 items) [78]
**Tertiary outcomes**		
	Program satisfaction	Likert scale developed for the study to assess satisfaction with the assigned condition and the overall study (11 items)
	Program engagement	Likert scale developed for the study to assess completion of daily practice, completion barriers and facilitators, and intention to complete practice in the following week (6 items)

**Table 4 table4:** Standard Protocol Items Recommendations for Interventional Trials (SPIRIT) schedule of enrollment, interventions, and assessment.

Study activities in each phase		Timepoint				
		Enrollment	Postallocation			
		Week 1 (t0)	Week 2	Week 9	Week 10 (t1)	3 months postpartum (t2)
**Preintervention**						
	Eligibility screening	X^a^	N/A^b^	N/A	N/A	N/A
	Informed consent	X	N/A	N/A	N/A	N/A
	Allocation	X	N/A	N/A	N/A	N/A
**Intervention**						
	Web-based mindfulness training	N/A	X	X	N/A	N/A
	Web-based loving-kindness and compassion training	N/A	X	X	N/A	N/A
	Web-based progress muscle relaxation	N/A	X	X	N/A	N/A
**Assessments**						
	Demographics	X	N/A	N/A	N/A	N/A
	Self-reported mental well-being, depression, anxiety, self-compassion, mindfulness, and quality of life	X	N/A	N/A	X	X
	Self-reported affect, stress, and emotion regulation	X	N/A	N/A	X	X
	Program engagement	N/A	X	X	N/A	N/A
	Interviews	N/A	N/A	N/A	X	X

^a^X denotes when the study activity occurs.

^b^N/A: not applicable.

#### Data Management

On enrollment, all participants will be given a unique identifier that will be used in all database records. Although patient identifying information (first name and initials, date of birth, phone number, and email address) will be collected, this information will be stored separately to the outcome data and will be linkable only by the RA. Identifying information will be used for patient contact and linking with ORIGINS records.

### Analytic Plan

#### Quantitative Analysis

The baseline characteristics of the participants will be reported to describe the sample. Descriptive statistics will be used to summarize the quantitative data collected for each feasibility domain. Feasibility metrics will address the ADePT (*a process for decision making after pilot and feasibility trials*) framework [79]. This feasibility framework has been incorporated as part of a phased approach to the development and evaluation of the intervention. Feasibility assessment will use both quantitative feasibility data and qualitative data derived from the postprogram interviews. According to the ADePT framework, the progression criteria to move from a pilot to full-scale trial are divided into 3 categories: green, red, and amber (Table 5). Although the purpose of the study is not hypothesis testing, we will calculate the differences between the experimental groups and the control condition for primary and secondary outcomes.

**Table 5 table5:** Decision-making criteria for full-scale randomized controlled trial, adapted from the “a process for decision making after pilot and feasibility trials” framework.

Outcome	Metrics
Green (proceed to full-scale RCT^a^ without refinement)	≥50% of eligible participants consent to the pilot trial ≥70% of consented participants commence each intervention arm ≥50% of consented participants complete all intervention sessions in each intervention arm Program satisfaction ratings and postprogram interventions demonstrate high satisfaction and acceptability of the program for ≥50% participants
Red (do not proceed to full-scale RCT)	<30% of eligible participants consent to the pilot trial <20% of consented participants commence each intervention arm Program satisfaction ratings and postprogram interventions demonstrate low satisfaction or lack of acceptability of the program for ≥50% participants
Amber (consider proceeding to full-scale trial only after protocols have been refined)	Neither red nor green criteria were met. Findings from qualitative and quantitative data will be used to determine whether a full-scale RCT should proceed with revisions

^a^RCT: randomized controlled trial.

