### Web-Based Meditation-Based Interventions

There are a number of potential benefits of delivering MBIs and CBIs via the internet [52,54], such as the capacity to implement across populations, to reach individuals who might struggle to access face-to-face services, the potential to improve cost-efficiencies, and the ability to provide greater flexibility to service users [55]. Meta-analyses have found small-to-moderate effect sizes for web-based and self-guided MBIs in promoting well-being and reducing symptoms of psychological distress [56]. Although there are limited studies of internet-delivered CBIs, 1 RCT of web-based compassion training for self-critical individuals reported moderate-to-large effect sizes for reductions in distress, relative to usual care [57]. However, it is currently unclear whether MBIs and CBIs delivered on the web are a feasible and efficacious means of reducing stress and promoting well-being in the perinatal period [58]. Available evidence for internet-delivered MBIs highlights some issues with intervention feasibility. For example, 1 RCT found evidence that compared with waitlist control, a web-based, 8-week self-guided MBI was associated with significant reductions in stress and pregnancy distress among pregnant women who completed the intervention; however, attrition exceeded 50% [59]. In the study by Kelman et al [52] on web-based CBI versus web-based CBT for perinatal women and those planning pregnancy, retention at a 2-week follow-up was 62% for CBI versus 71% for CBT.

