#### Sample Size

We aim to recruit 25 participants per treatment arm (75 participants in total). The recommended sample sizes per treatment arm for pilot trials are between 15 and 25 when the standardized effect sizes for outcomes in the main trial are expected to be medium (0.5) to small (0.2) [63].

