### Interventions

All intervention conditions will be delivered on the web using the Teachable platform. The program is structured so that each day of the intervention is delivered as a separate *lesson*. The same intervention structure will be used for each condition: 8 weeks, with 1 formal practice (audio recording) to be practiced daily each week. Participants will also receive text instructions for 1 informal practice each week, which they are encouraged to practice as often as feasible. The informal practices are designed to support participants to integrate skills and learning into their daily activities.

Both the mindfulness training and LKCT interventions were developed following a two-step process. First, we conducted a scoping review of the literature to determine key components of MBIs and CBIs administered during the perinatal period. In addition to extracting data regarding intervention characteristics (eg, weekly themes, duration, mode of delivery, home practice), we also extracted data regarding specific considerations for delivering meditation-based interventions during pregnancy. These data were used to develop a draft intervention protocol for the mindfulness training and LKCT conditions. The protocol was developed by AF and AO, who have masters-level training in clinical psychology and are both certified teachers of MBIs and CBIs. The PMR condition was based on exercises described by Jacobson [65] and adapted for pregnancy by excluding muscle tension in the abdominal area.

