### Data Collection

#### Study Outcomes

We will assess several metrics to determine the feasibility of the study across the following domains: recruitment, randomization, retention, and adherence (Table 2). To assess the feasibility of the assessment battery and calculate standard deviations on the measures, the main outcome measures for the full-scale RCT will be used (Table 3). Postintervention interviews will be conducted with a randomly selected sample of participants (n=approximately 15 in each condition) to gather further data on engagement with practice, reasons for attrition, satisfaction with the program, enjoyment and value of the program, and barriers and facilitators to engagement. Participants will be invited to partake in a semistructured interview by telephone, videoconference, or at the JHC clinic. Table 4 shows the Standard Protocol Items Recommendations for Interventional Trials (SPIRIT) schedule of enrollment, interventions, and assessment.

**Table 2 table2:** Summary of outcomes and metrics for pilot study.

Outcome	Metrics
Recruitment	Number of participants screened per week Number of participants enrolled per week Proportion of recruited ORIGINS participants electing to enroll
Randomization	Proportion of eligible participants who access the web-based intervention following randomization Proportion of eligible participants who complete at least one session (one day) of the web-based intervention
Retention	Proportion of participants that complete t0 (baseline) measures after commencing them Condition-specific completion rates following randomization (completion defined as ≥50% of modules accessed at least once) Proportion of participants commencing baseline measures that complete time 1 (posttest) and time 2 (follow-up) measures
Adherence	Self-reported completion of practice Lesson completions in Teachable program
Acceptability	Proportion of participant opt-outs from each intervention condition Proportion of participant withdrawals from the study Self-reported intervention and study satisfaction

**Table 3 table3:** Summary of outcomes and measures for a full-scale randomized controlled trial.

Outcomes		Measures

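### The Green completion criterion in Table 5 requires every daily lesson, while Table 2 counts half the modules opened once as completion, and the two are not reconciled

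*Protocol article*

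**What the plan says.** The progression rule is in Table 5 (Analytic Plan, Quantitative Analysis). One of the four Green conditions is "≥50% of consented participants complete all intervention sessions in each intervention arm". Red contains no completion condition. Amber covers everything that is neither Red nor Green.

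Table 2 (Data Collection, Study Outcomes) lists, under Retention, "Condition-specific completion rates following randomization (completion defined as ≥50% of modules accessed at least once". Under Adherence it separately lists "Lesson completions in Teachable program".

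Three passages fix what a session is:
- Interventions says that "each day of the intervention is delivered as a separate" lesson.
- The same section sets the structure as "8 weeks, with 1 formal practice (audio recording) to be practiced daily each week".
- The Randomization row of Table 2 counts women who "complete at least one session (one day) of the web-based intervention".

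The word module is not defined anywhere or related to session or lesson.

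On size, Sample Size says "We aim to recruit 25 participants per treatment arm (75 participants in total". On expectations, the introduction's section on web-based programs describes an 8-week self-guided mindfulness program in pregnancy in which "attrition exceeded 50" per cent.

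**The concern.** Feasibility is the pilot's first objective, completion by arm is one of the measures named for it, and the article presents its prespecified progression criteria as a strength. Yet the completion condition that decides Green does not use the completion measure that the article defines. A woman who finishes 55 of 56 lessons is a completer in Table 2 and a non-completer in Table 5.

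Two things follow. The same data could support a yes or a no on this condition, depending on which table the reader applies, and settling that after the data are in would undo the prespecification. Also, taken literally, a few missed daily lessons per woman could move a well-used program from Green to Amber, which calls for refinement before the main trial, although nothing about the program proved infeasible.

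**Working it through.** **1. The plan's own figure.** 3 arms × 25 = 75, as stated. The arm size comes from a cited rule for pilot trials, not from a calculation on completion.

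**2. What all sessions means.** One session is one day, and each day is a lesson. 8 weeks × 7 days = 56 lessons. The article does not print 56; it follows from the three passages above.

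**3. The two standards side by side.**

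| | Table 5, Green | Table 2, Retention |
|---|---|---|
| Amount | all | at least half |
| Action | completed | accessed once |
| Unit | session (one day) | module (undefined) |
| Denominator | consented | after randomization |

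If a module is a daily lesson, Table 2 requires 56 / 2 = 28 opened once. If a module were a week, it would require 8 / 2 = 4. The article does not say which.

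The Table 5 denominator has its own difficulty. Consent comes before screening, and randomization follows the baseline battery. A woman who consents but is not randomized belongs to no arm, so consented women cannot be counted arm by arm. The calculation below takes 25 randomized women per arm as the denominator.

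**4. Chance of meeting the Green completion condition.** 50% of 25 is 12.5, so at least 13 women are needed in each arm. Let p be the true proportion who complete all 56 lessons, the same in each arm, with arms independent. Per arm the chance is P(X ≥ 13), X ~ Binomial(25, p). For all three arms it is that value cubed. The article gives no p, so a range is assumed.

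| Assumed p | One arm | All three arms |
|---|---|---|
| 0.30 | 1.75% | < 0.01% |
| 0.40 | 15.4% | 0.4% |
| 0.50 | 50.0% | 0.5³ = 12.5% |
| 0.60 | 84.6% | 60.6% |
| 0.70 | 98.25% | 94.9% |

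An 80% chance needs p of about 0.64. These figures concern this condition alone. Green has three others, so the chance of Green overall cannot be higher.

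**5. How far apart the two standards are (illustration only).** Let q be an assumed chance of completing any one lesson, with lessons independent. All 56 has probability q^56; at least 28 of 56 is a binomial tail. The second column treats a module as a lesson and access as completion.

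| q | All 56 | At least 28 of 56 |
|---|---|---|
| 0.60 | about 0 | 95% |
| 0.90 | 0.27% | about 100% |
| 0.95 | 5.7% | about 100% |
| 0.98 | 32% | about 100% |

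For half the women to complete all 56, q must be 0.5^(1/56) = 0.988. Independence overstates the difficulty, because adherence clusters within women. At the same average completion, more women would finish everything than this model predicts.

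**The case against.** A high bar for going ahead with no changes at all is defensible. Table 5 spells out its own standard and does not borrow Table 2's definition, and the logged lesson completions under Adherence can supply the count. Missing the condition stops nothing: Red is unaffected, and under Amber the team weighs qualitative and quantitative findings. The team also took steps to improve engagement, with consumer testing, shorter practices in weeks 1 and 2, weekly text reminders and a login call. All of this stands, and it limits the consequence.

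Three stronger readings are tempting, and the article does not support them.
- **That Green is practically out of reach.** No expected all-lesson rate is given, and over assumed rates of 0.30 to 0.70 the chance runs from about 0% to 95%. The cited attrition belongs to another program and measures attrition, not lesson completion. It makes a 50% all-lesson target look ambitious but does not fix p.
- **That the two completion figures contradict each other.** They carry different labels, one a retention metric and the other a progression condition. They will very probably differ, which is not in itself a contradiction.
- **That the authors meant the Table 2 definition to govern Green.** Nothing says so. Table 5 says all, and that may be deliberate.

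The objection does not explain why one article measures completion in two ways that differ on four counts, or how consented women are to be counted within an arm.

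**Conclusion.** The point holds as an unreconciled definition in a decision rule. Both standards are printed in the article, so this is not detail left to a fuller document. Read literally, Green requires at least 13 of 25 women in every arm to complete all 56 lessons. If the all-lesson rate stays below 50%, as the cited attrition suggests it might, the chance that all three arms pass is below 12.5%. It becomes better than even only as the rate approaches 60%, and reaches 80% at about 64%. These figures assume equal rates across arms, independent arms and 25 randomized women in each. The harm is a possible Amber that reflects wording and not infeasibility, together with room to choose a definition after the results are known. The trial is not stopped, and no estimate is biased.

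**What to change.** Before enrollment, align Tables 2 and 5 on three items:
- **Unit:** Teachable daily lessons, with module defined in those terms.
- **Completion:** one definition, saying whether a lesson counts when opened or when finished, and how many lessons are needed.
- **Denominator:** women randomized to the arm. This is a deliberate change from consented women in Table 5 and should be stated as such.

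The simplest route is to base the Green condition on the Table 2 definition. If a stricter level is intended for Green, give it as an explicit number of lessons and justify it. Either way, report the full distribution of lessons completed by arm, so that readers can see how the result depends on the cut-off.

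The cost is a wording change to two tables. Lesson completions are already to be collected, so no new data are needed. The downside of adopting the Table 2 definition is a Green standard that looks less strict.

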#### Qualitative Analysis

Qualitative data collected during interviews will be analyzed to identify key themes regarding program engagement, acceptable and perceived impacts, and confidence in sustaining meditation practices. Using the approach by Braun and Clarke [80] to thematic analysis, transcripts will be iteratively coded, and codes will be collated into higher-level themes [80]. Transcripts will be reviewed to identify all instances of thematic codes, with codes expanded or collapsed as required. Qualitative data will be analyzed using qualitative content analysis [81], assigning a code to each concept using NVivo. Similar concepts will be identified and categorized into categories. Data will be analyzed using a phenomenological approach (ie, as a description of experiences as consciously experienced by participants), and narrative themes will be deducted until saturation. The coding process will be guided by the following deductive constructs: intervention acceptability, engagement, and application; mental health and well-being experiences; and suggestions for program revision.

### Data Monitoring and Harms

Adverse events will be monitored weekly based on the self-reported data provided by participants at the weekly assessment and the data collected by the ORIGINS team. The key adverse event linked to the MMM study is deteriorating mental health; however, there is also a range of potential adverse events linked to pregnancy that are recorded by ORIGINS. In the MMM study, participants will be encouraged to contact the RA at any point if they have concerns about deteriorating mental health. They are asked weekly if they wish to continue with the program. If they select “no,” they are asked about their reasons for discontinuation (including concerns about their mental or physical health). If participants report concerns about their mental health during the intervention or upon withdrawal from the study, they will be screened for depressive symptoms using the EPDS and for symptoms of traumatic stress using the abbreviated version of the Posttraumatic Stress Disorder Checklist–Civilian version (PCL-C) [82]. Participants who endorse item 10 on the EPDS or score 14 or more on the abbreviated PCL-C will receive a follow-up phone call from the study psychologist to discuss referral to more intensive or specialized support services. If a participant reports concerns about their mental or physical health, this will be reported to ORIGINS. ORIGINS has standard operating procedures for following up adverse events [62]. All adverse events in the MMM study will be recorded on an adverse event monitoring form, and all events and follow-up will be reported to an independent study monitor.

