## Introduction

### Background

Maternal mental health in pregnancy is an issue of substantial public health importance [1]. Anxiety and depression are the most common postpartum difficulties experienced by women globally [2], with an average prevalence of 10% to 15%, although rates as high as 64% have been reported in US samples [2]. Psychological distress during pregnancy is associated with adverse impacts for both the mother and child [3-6]. For example, prenatal symptoms of depression and anxiety are associated with impaired fetal growth [7], risk of child emotional and behavioral problems [8-13], and differences in child brain morphology [14]. These findings align with the Developmental Origins of Health and Disease model [15], which posits that the characteristics of the perinatal environment exert lifelong influences on offspring health risk and resilience. Maternal mental health difficulties in pregnancy can also increase the risk of adjustment difficulties in the postnatal period [16,17].

Despite the availability of accessible and effective treatments for mood disorders, approximately half of the women experiencing perinatal distress do not seek help [18-20]. Such findings demonstrate a need for universal mental health promotion efforts that complement targeted treatment programs and span prevention through early intervention. Nonpharmacological approaches to mood management are also preferred by pregnant women because of concerns about the effects of pharmacological interventions on the developing fetus [21]. Furthermore, research on mental health risk and resilience also illustrates the dual benefits of targeting subclinical symptoms of distress and increasing positive mental health and well-being. For example, although a history of psychiatric symptoms predisposes individuals to future psychopathology, positive mental health both supports recovery from distress and protects against poor mental health in the future [22-25]. Studies with pregnant women have found that prenatal positive mental health traits such as positive affect and optimism are protective of postpartum depression [26,27] and birth outcomes such as preterm delivery [28]. A dual approach aligns with two-factor models of mental health, which recognize distress and well-being as 2 distinct but interrelated continua [22,29,30].

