### Participants

#### Eligibility Criteria

Eligible participants are pregnant women participating in the ORIGINS project (ORIGINS) and receiving antenatal care at a metropolitan health campus (JHC). ORIGINS is a longitudinal birth cohort study that recruits pregnant women and their partners from 12 weeks of gestational age and follows them and their child until 5 years postpartum. ORIGINS is open to any women who are birthing their baby at JHC [62]. Participants considered for inclusion in the MMM study will be women (1) at 18 to 30 weeks of pregnancy; (2) aged ≥18 years; (3) able to read, write, and understand English; and (4) able to access the internet.

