### Participant Procedure

Once a participant has been randomized, the RA will add the participant to their allocated intervention condition in Teachable, the web-based system used to deliver the programs. Participants will then receive an automated email from Teachable prompting them to create a password. Participants will also receive a phone call from the RA to confirm that they have successfully logged in to the program and to answer any participant questions. Participants will be asked to nominate a start date for the program within the next week.

Participants will access their allocated condition within the MMM program either on a computer (via the Teachable website) or on a smart device via the Teachable app. On the basis of their nominated start date, participants will receive an automated weekly text message with a link to the weekly outcome measures. These measures involve self-reports of stress, affect, and emotion regulation and are also designed to prompt self-reflection. There are also questions about daily practice, intentions to continue practice, and barriers and facilitators to practice. Participants who indicate that they do not intend to continue practice in the next week will be asked if they wish to opt out of the program. Participants choosing to opt out will be directed to a survey, which will ask them about the reasons for opting out of the program and request program feedback. At the conclusion of the 8-week intervention period, participants will be emailed a link to the t1 (posttest) assessment battery. Participants will be emailed again with a link to the t2 (follow-up) assessment battery 3 months after giving birth.

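### After the 8-week program the article describes no scheduled adverse event query up to t2, and its safety screening step leaves out program completers who report deterioration

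*Protocol article*

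**What the plan says.** **Sources of adverse events.** Data Monitoring and Harms names two: the participant's weekly self-report, reviewed weekly, and data gathered by the ORIGINS team. Worsening mental health is the key event for this study. There is also an open route: "participants will be encouraged to contact the RA at any point if they have concerns about deteriorating mental health".

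**Screening step.** The same section then says: "If participants report concerns about their mental health during the intervention or upon withdrawal from the study, they will be screened for depressive symptoms". Screening uses the EPDS and an abbreviated PCL-C, with a psychologist's call for certain answers.

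**Timing.** Under Participant Procedure the weekly survey links are sent by reference to the start date the woman chooses. Then: "At the conclusion of the 8-week intervention period, participants will be emailed a link to the t1 (posttest) assessment battery". Later: "Participants will be emailed again with a link to the t2 (follow-up) assessment battery 3 months after giving birth". Table 4 puts t0 in week 1, the program in weeks 2 to 9, t1 in week 10 and t2 at 3 months postpartum.

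**Later measurements.** Table 4 repeats the self-reported depression and anxiety measures at t1 and t2 and marks interviews at both. Table 3 lists the EPDS and the anxiety scale as secondary outcomes. Data Monitoring and Harms does not name the t1 or t2 batteries as a source of adverse events.

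**The concern.** Two features of the harms section do not fit the length of follow-up.

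First, the only scheduled question by which the study itself asks about harm is the weekly one, and it is built around whether the woman wishes to continue the program. Once the program is over, that question has no described successor, although she remains in the study until 3 months after birth.

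Second, the invitation to report concerns has no time limit, but the screening step does. A completer who has not withdrawn and who calls the research assistant in late pregnancy or after birth has used a route the article offers, yet meets neither condition for screening.

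At stake is how complete the harm record is by arm. After the program it would depend on women volunteering information and on what the parent cohort happens to record. The Background section gives a reason to care about this period: "Maternal mental health difficulties in pregnancy can also increase the risk of adjustment difficulties in the postnatal period". The Strengths section presents the measurement of harm as an asset of the trial, and the pilot is meant to test methods for the full-scale trial, so an undefined harm window would carry forward.

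**Working it through.** The article gives no length for the interval after the program, so there is no stated figure to reproduce. The interval follows from the schedule and an assumed week of birth.

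**Inputs from the article**
- Gestational age at entry, G: "at 18 to 30 weeks of pregnancy" (Eligibility Criteria), so 18 to 30.
- Delay before starting, d: 0 to 1 week, from "Participants will be asked to nominate a start date for the program within the next week" (Participant Procedure).
- Program length: 8 weeks. Table 4 agrees: weeks 2 to 9 inclusive are 9 − 2 + 1 = 8.
- t2: 3 months after birth, taken as 13 weeks.

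**Assumption**
- Gestational age at birth, B. The article gives none; 40 weeks is the central value, with 37 to 41 as the range.

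**Formula**

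Program end = G + d + 8. Interval to t2 = (B − program end) + 13.

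| B | G | Program end (d = 0; d = 1) | Weeks to birth | Weeks to t2 |
|---|---|---|---|---|
| 40 | 18 | 26; 27 | 14; 13 | 27; 26 |
| 40 | 30 | 38; 39 | 2; 1 | 15; 14 |
| 37 | 18 | 26; 27 | 11; 10 | 24; 23 |
| 37 | 30 | 38; 39 | −1; −2 | 12; 11 |
| 41 | 18 | 26; 27 | 15; 14 | 28; 27 |
| 41 | 30 | 38; 39 | 3; 2 | 16; 15 |

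Birth at 40 weeks gives 14 to 27 weeks. Birth at 39 to 40 weeks with no starting delay gives the same range: for B = 39 and d = 0 the values are 39 − 26 + 13 = 26 and 39 − 38 + 13 = 14. A full week's delay with birth at 39 lowers the floor to 13. Over 37 to 41 weeks the range is 11 to 28.

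The negative entries show that the interval does not always contain birth. With birth at 37 weeks, delivery comes before program end if G + d + 8 > 37, that is, for entry after 29 weeks with no delay or after 28 weeks with a one-week delay.

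**The text on reporting and screening, by situation**

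| Situation | May contact the research assistant | Inside the screening step |
|---|---|---|
| In the program | Yes | Yes |
| At withdrawal | Yes | Yes |
| Completed, still in follow-up to t2 | Yes | No |

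The third row is the gap.

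**The case against.** The strongest reply is that the harm the article names as key is in fact measured after the program. The EPDS and the anxiety scale are given at t1 and t2, and interviews are marked at both. ORIGINS is an express second source: it records pregnancy-related events, has its own follow-up procedures and continues to 5 years postpartum. Two further rules carry no end date: reported health concerns are passed to ORIGINS, and all adverse events go on a form and to an independent monitor. This stands. A reader might infer that the study plans no harm collection after week 9; the article does not support that.

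A reader might also divide the 8 program weeks by total follow-up and conclude that roughly two thirds to three quarters of it is uncovered. That sum gives no credit to t1, t2 or ORIGINS and should not be used.

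Nor do the two sentences on reporting and screening contradict each other outright. One governs contact, the other an additional step, and both can be followed. What remains is that the step is silent on a situation the first sentence invites.

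The evidence from Table 4 is also limited. It does not show the weekly adverse event query at all, nor the weekly stress, affect and emotion regulation measures described in the text. Week 9 as the end of weekly monitoring is therefore an inference from the schedule, and the full protocol may define a reporting period.

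Finally, the Background sentence concerns background risk, not delayed harm from the program, and closer monitoring during exposure is a defensible choice in a pilot of 75 women.

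These replies narrow the point without removing it. Repeated outcome scores are not adverse event ascertainment unless the plan says so, open contact depends on the woman, and the article does not say that ORIGINS asks about worsening mental health between t1 and t2. The limit on the screening step is stated in the article itself.

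**Conclusion.** The point holds as a modest, inexpensive improvement. As described, no scheduled adverse event query follows the program, and the screening step excludes a completer who reports deterioration before t2. The interval concerned is about 14 to 27 weeks under an assumed birth at 40 weeks, or 11 to 28 weeks for birth at 37 to 41 weeks. It contains birth for most women but not for some of the latest entrants, and it is partly covered by t1, t2, participant-initiated contact and ORIGINS. The conclusion rests on reading the weekly surveys as confined to the program, which the schedule implies but does not state, and on the condensed article being the only document available.

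**What to change.** - State that the study's adverse event period runs from randomization to t2.
- Add the existing question on mental or physical health concerns to the t1 and t2 batteries, covering the time since the previous assessment. Record answers on the adverse event form and send them to the independent monitor.
- Report events by arm, separately for the program period and for the time after it.
- Have the sponsor reconcile the two sentences in Data Monitoring and Harms on open-ended contact and on when screening applies, so that the research assistant has one rule for concerns raised after the program. What that clinical response should be is for the sponsor to settle.

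The cost is one item in each of two batteries already being sent, plus a wording amendment. The downside is that some late events unrelated to the program will be recorded; the separate reporting by period helps in reading them.
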